## Abstract

**Background:**

Obesity and stress are among the most common lifestyle-related health problems. Most of the current disease prevention and management models are not satisfactorily cost-effective and hardly reach those who need them the most. Therefore, novel evidence-based controlled interventions are necessary to evaluate models for prevention and treatment based on self-management. This randomized controlled trial examines the effectiveness, applicability, and acceptability of different lifestyle interventions with individuals having symptoms of metabolic syndrome and psychological distress. The offered interventions are based on cognitive behavioral approaches, and are designed for enhancing general well-being and supporting personalized lifestyle changes.

**Methods/Design:**

339 obese individuals reporting stress symptoms were recruited and randomized to either (1) a minimal contact web-guided Cognitive Behavioral Therapy-based (CBT) intervention including an approach of health assessment and coaching methods, (2) a mobile-guided intervention comprising of mindfulness, acceptance and value-based exercises, (3) a face-to-face group intervention using mindfulness, acceptance and value-based approach, or (4) a control group. The participants were measured three times during the study (pre = week 0, post = week 10, and follow-up = week 36). Psychological well-being, lifestyles and habits, eating behaviors, and user experiences were measured using online surveys. Laboratory measurements for physical well-being and general health were performed including e.g. liver function, thyroid glands, kidney function, blood lipids and glucose levels and body composition analysis. In addition, a 3-day ambulatory heart rate and 7-day movement data were collected for analyzing stress, recovery, physical activity, and sleep patterns. Food intake data were collected with a 48 -hour diet recall interview via telephone. Differences in the effects of the interventions would be examined using multiple-group modeling techniques, and effect-size calculations.

**Discussion:**

This study will provide additional knowledge about the effects of three low intensity interventions for improving general well-being among individuals with obesity and stress symptoms. The study will show effects of two technology guided self-help interventions as well as effect of an acceptance and value–based brief group intervention. Those who might benefit from the aforesaid interventions will increase knowledge base to better understand what mechanisms facilitate effects of the interventions.

**Trial registration:**

Current Clinical Trials NCT01738256, Registered 17 August, 2012.

## Background

Obesity is increasing globally and is correlated with a variety of health problems. Consequences of being overweight might result in the metabolic syndrome, which is a set of medical features such as impaired glucose metabolism, dyslipidaemia and hypertension that are risk factors for cardiovascular disease and type-II diabetes [1,2]. Lifestyle changes have proven to be an efficient way to counter obesity and related disorders [3,4], however it is challenging to achieve long-term lifestyle changes using limited resources in real-life health care systems.

Individuals having problems related to overweight also experience additional health issues such as stress. Psychological stress is known to be related with increased body mass. In addition psychological stress also contributes to weight gain [5-7]. The fourth European Survey of Working Conditions reported that 22% of working European individuals suffers from stress. It is important to note that the annual financial cost for work-related stress within the EU was estimated at €20,000 million [8].

Much of existing health service models have problems in supporting long-term lifestyle changes required for managing of weight and stress. In addition, existing disease prevention and management models are not cost effective and do not necessarily reach those individuals who need them the most. A large number of studies indicate that lifestyle changes could be promoted by using different types of Internet-based technologies [9-14]. Available literature provides significant evidence that supports the effectiveness of web-based interventions of lifestyle and behavioral changes [15,16], however what type/s of web-based interventions could be beneficial for individuals with chronic health disorders is vaguely reported and need further investigation. In addition, little is known about the relevance of low intensity programs using novel interactive technologies offering minimal contact for those reporting both obesity and stress.

Additional controlled studies are necessary to evaluate different types of low intensity intervention models for prevention and treatments based on self-management. There are several options to facilitate development of low intensity self-management approaches for lifestyle-related chronic conditions, for example, use of Internet-administrated assessment, online health screening and coaching approaches based on current knowledge of Cognitive Behavioral Therapies (CBT). Low intensity CBT-based interventions use a minimum level of intervention essential to enhance mental health and well-being [17]. Much of the low intensity interventions use novel interactive communication technologies. They might support long-term lifestyle changes because they deliver swift and easy access to early intervention and preventive programs.

In addition to investigating the effect of low intensity web-based health screening and coaching application, we wanted to explore the effect of third wave CBT methods by applying mindfulness and acceptance-based interventions for individuals with obesity and stress. There has been an increasing interest towards these novel approaches lately with an aim to improve psychological flexibility for promoting life style changes. It has been proposed that psychological flexibility is one of the key requisites for psychological health [18]. Psychological flexibility is reflected by how a person: adapts to inconsistent situations, reconfigures mental resources, modifies viewpoints, and balances competing desires and needs. For example, interventions that include components of psychological flexibility have demonstrated significant benefits when compared with controlled conditions on measures of depression and anxiety [19]. Additionally, there is evidence suggesting that lower psychological flexibility and burnout increase the risk of unstable emotional state of mind and adverse eating habits [20]. These results among others indicate that improvement of psychological flexibility is undoubtedly beneficial for individuals suffering from obesity and/or stress.

Mindfulness, acceptance and value-based methods targeting psychological flexibility include psychological interventions such as Acceptance and Commitment Therapy (ACT) [21]. There are few studies that have investigated the effect of novel mindfulness and acceptance-based interventions such as ACT for chronic health conditions [22,23]. An increasing number of studies indicate that ACT is conceivably effective for a wide range of psychological and health disorder, such as chronic pain, smoking, diabetes, epilepsy and work-related stress [24,25]. Yet further studies are desirable to prove the effectiveness of ACT-based interventions such as mindfulness and acceptance practices in improving deteriorated metabolic indicators, such as dyslipidemia, low-grade inflammation or deficiencies in glucose metabolism.

ACT has mainly been investigated using face-to-face interventions, and there are only few studies that have studied the effect of ACT-based approaches for health disorders using web or mobile-based interventions. Web-based ACT interventions have been developed e.g. for tinnitus distress [26], chronic pain [27], and psychological stress [28]. Furthermore, ACT-based mobile apps have been studied on small scale [29,30]. To the best of our knowledge, there are very few controlled trials that have been conducted to investigate the effectiveness of ACT-based mobile interventions [29]. Overall, there are a limited number of controlled studies that have investigated the effects and feasibility of smartphone solutions for chronic health disorder [31].

### Aim and main hypotheses

The overall aim of the present study was to investigate the effect of three novel low intensity psychological interventions for metabolic syndrome risk factors, psychological flexibility and general well-being among obese individuals experiencing stress. The purpose was to study (a) the effects of minimal contact web-based CBT intervention including an approach of health assessment and coaching methods (Internet), (b) the effects of mobile-based intervention containing mindfulness, acceptance and value-based exercises (Mobile), and (c) the effects of face-to-face group intervention using mindfulness, acceptance and value-based approaches (Face-to-Face) in a controlled study design, where control (Control) received no treatment, but the same measurements were completed for all the groups. Thus, both technology-based low intensity self-help interventions offered minimal contact, and they were compared to a brief group intervention. Moreover, we were interested in studying acceptability, applicability, perceived benefits, user experiences, and usage of the said interventions.

The three interventions groups, and the control group were compared based on changes in lifestyle measures (e.g. food and nutrition intake, meal patterns, physical activity, sleeping habits), psychological measures (e.g. psychological flexibility, perceived stress, depression symptoms, quality of life, perceived quality and quantity of sleep), clinical and biochemical variables (e.g. BMI, body composition, circulating glucose, insulin, lipids, stress and inflammation indicators), other physiological measurements (e.g. objective sleep measurements, heart rate variability-based recovery from stress), and user experiences (e.g. experiences with the interventions, actual usage, realization of exercises presented in interventions). We formulized the following hypotheses:

H1: Participants who receive any of the three interventions would show improvements in lifestyle and psychological measures, and clinical, biochemical, and physiological variables as compared to the control group. Each intervention group is compared with the control condition separately.

H2: Participants who receive any of the three interventions will show equal positive changes in lifestyle, and psychological measures, and clinical, biochemical, and physiological variables when the interventions are compared with each other.

We also wanted to examine demographics and psychological variables that could predict change over time (Pre, Post and Follow-up) including age, gender, initial BMI, physical activity, psychological flexibility, stress and depressive mood and psychological symptoms. Further, we would examine potential mediators on the effect of the interventions including psychological flexibility and mindfulness skills. Secondary objectives include analyses of the user experiences and validity of used measurement and intervention methods.

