### Statistical analysis

Data will be analyzed using the IBM SPSS statistics version 19.0 or newer and Mplus statistical package 7.1 [70]. Analyses will be controlled for possible baseline differences between the groups. Differences in the stability of the outcome measures between the groups will be examined using multiple-group modeling techniques. Full information maximum likelihood (FIML) estimation under the assumption of data missing at random (MAR) will be used in analyzing incomplete data. As the normality assumption is violated, maximum likelihood with robust standard errors (MLR) will be used. The significance level of the study will be set at 0.05. Cohen’s *d* will be used to estimate the effect size, and to reflect the clinical significance of the interventions. A between group effect size of 0.2 is considered small, 0.5 medium, and 0.8 large [71]. A within group effect size of 0.5 is considered small, 0.8 medium, and 1.1 large.

Power calculations were performed in order to determine the sufficient sample size to detect the significant intervention effect at a significance level of α = 0.05. Analysis was conducted for one of the primary outcome measures, depression symptoms (BDI-II). On the bases of our earlier studies using similar brief intervention procedures [72] we expect that the Post-measurement difference between the intervention and control group to be approximately 10 scores. A sample size of 320 (80–85 per group) was expected be sufficient at the power level of 1.00.

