## Discussion

### The aim of the study

This article demonstrates a research protocol for a randomized controlled trial for studying different well-being programs among individuals with metabolic syndrome risk factors and perceived stress. The effects of three low intensity psychological interventions were investigated in a randomized controlled study design. We expect that the effect of a minimal contact web-based health assessment and coaching methods, and the effect of mobile-based intervention containing mindfulness, acceptance, and value-based exercises would be equal to the effect of face-to-face group intervention using mindfulness, acceptance, and value-based approaches. Further, we expect that these low intensity interventions would show larger changes in psychological and physical measurements of health and well-being when compared with the no treatment control group.

Examining the effects of low intensity interventions with reasonable cost-effectiveness is essential when we are dealing with common health problems. Both obesity and stress related issues are among the major health concerns at the moment [8,73]. In addition to the fact that lifestyle related health problems are very common, the current health service models face several challenges. For example, it has been reported that only a minority of individuals who may benefit from effective health services aiming at lifestyle changes actually use them or seek professional help [74,75]. Further, Internet contains self-help web pages and programs dealing with health and chronic health problem, but relatively few of them are based on evidence-based interventions. Thus, evidence-based low intensity interventions to which individuals have 24/7 access are feasible option to solve or prevent these problems [17]. Also, the development of interactive technologies expands opportunities to provide low intensity interventions, although more knowledge is necessary to verify their effectiveness and acceptability. Further, it is important to evaluate the effects of self-help and low intensity interventions regarding their effects both on psychological and physiological variables.

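### H2 predicts equal change across the three interventions, but the plan has no analysis that can support equality: no margin, no interval rule and no sample-size basis for that comparison

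*Protocol article*

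**What the plan says.** Under Aim and main hypotheses, the protocol article states two hypotheses. H1 compares each intervention with control. H2 compares the interventions with one another and predicts that participants "will show equal positive changes in lifestyle, and psychological measures", and likewise in clinical, biochemical and physiological variables. The Discussion (The aim of the study) repeats this for the web and mobile arms, whose effects "would be equal to the effect of face-to-face group intervention using mindfulness, acceptance, and value-based approaches".

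The Statistical analysis section contains four elements that could bear on H2:

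- **Method:** "Differences in the stability of the outcome measures between the groups will be examined using multiple-group modeling techniques".
- **Level:** "The significance level of the study will be set at 0.05".
- **Effect size:** Cohen's d is to be used "to reflect the clinical significance of the interventions", with the benchmarks "A between group effect size of 0.2 is considered small, 0.5 medium, and 0.8 large".
- **Sample size:** 320 in total, 80-85 per group, at a stated power of 1.00. It rests on depression symptoms (BDI-II) and an expected "Post-measurement difference between the intervention and control group to be approximately 10 scores".

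The article gives no equivalence or non-inferiority margin, no confidence-interval rule and no sample-size calculation for a comparison between interventions.

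**The concern.** A test of difference can reject equality but cannot establish it. When the hypothesis is equality and the stated inference is a difference test, the only result compatible with the hypothesis is failure to reject. That result becomes more likely as the sample shrinks, the measurements get noisier or participants drop out. Imprecision then works in favour of H2, whereas under H1 it works against the hypothesis. The Limitations section itself warns that several features of the study might make differences between groups hard to detect.

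At stake is whether the trial may conclude that minimal-contact web or mobile delivery does as well as a psychologist-led group. A reader could draw that conclusion from non-significant comparisons even if the interventions differ.

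**Working it through.** **Inputs from the article.** Planned size is 80-85 per group. The number recruited is 339 over four groups, and 339/4 = 84.75. Alpha is 0.05. The benchmarks for d are 0.2, 0.5 and 0.8. The power calculation uses 10 BDI-II points, intervention versus control.

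**Assumptions, because the article gives no figure.** Two-sided testing, equal allocation, normal approximation and SD = 1 for differences on the d scale. Margins of 0.2 to 0.5 SD are shown as a range. Attrition is shown as none or 20% (0.8 × 85 = 68 per arm). A baseline correlation of r = 0.5 is used where stated.

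**1. The plan's own figure.** Power = Φ(10 / (SD·√(2/n)) − 1.96). No SD is stated, so 1.00 cannot be derived from the article alone. With n = 80:

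- SD 12: 10/(12 × 0.1581) = 5.27, power 0.9995.
- SD 14: power 0.995.
- SD 20: power 0.885.

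The result rounds to 1.00 for any SD up to about 13.9 (14.4 with n = 85). The figure is plausible, but it concerns H1 only.

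**2. What a difference test does for H2.** SE = √(2/n) = 0.158 (n = 80) or 0.153 (n = 85). The 95% CI half-width is 1.96 × SE = 0.31 or 0.30 SD. Power = Φ(d/SE − 1.96) + Φ(−d/SE − 1.96). Probability of a non-significant result:

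| True difference | n = 80 | n = 85 |
|---|---|---|
| 0.2 SD | 0.756 | 0.744 |
| 0.3 SD | 0.525 | 0.502 |
| 0.4 SD | 0.284 | 0.259 |
| 0.5 SD | 0.115 | 0.097 |

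**3. What an equivalence test could do.** Two one-sided tests (TOST) at 5% each correspond to a 90% CI lying inside ±m. With a true difference of zero, power = max(0, 2Φ(m/SE − 1.645) − 1), and n per arm for 80% power = 2·((1.645 + 1.282)/m)².

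| Margin m | n = 80 | n = 85 | n = 68 | n per arm for 80% |
|---|---|---|---|---|
| 0.2 SD | 0 | 0 | 0 | 429 |
| 0.3 SD | 0.199 | 0.244 | 0.083 | 191 |
| 0.4 SD | 0.624 | 0.664 | 0.508 | 108 |
| 0.5 SD | 0.871 | 0.894 | 0.796 | 69 |

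The zero at 0.2 SD arises because the 90% half-width (0.26 SD at n = 80, 0.25 SD at n = 85) already exceeds the margin.

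**4. Effect of baseline adjustment.** With r = 0.5, SE is multiplied by √(1 − 0.25) = 0.866. At n = 80 it becomes 0.1369, and for m = 0.4: 0.4/0.1369 = 2.92; 2.92 − 1.645 = 1.28; power 0.798. At 68 per arm the same calculation gives about 0.71.

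All these figures are for a single pair. H2 spans three pairs, and requiring all three to be equivalent lowers power further.

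**The case against.** The strongest reply is that the article nowhere says a non-significant result will be declared equality. H2 is a prediction, the Discussion words it as an expectation, and a prediction is not a decision rule. That stands. A reader might infer that the investigators will call H2 confirmed whenever a test fails, but the text does not say so. It supports only the statement that a null result could be used in that way and that no other inferential route to H2 is given.

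Second, 0.05 is not the whole of the inference, because between-group differences will also be sized by Cohen's d. This too is right and should be credited. But the benchmarks are descriptive labels. No value of d is named as small enough to count as equal, and a point estimate without an interval rule does not settle the matter. Nor does multiple-group modelling help by itself: an equality constraint that is not rejected is again a non-significant difference.

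Third, a condensed article may leave margins and interval reporting to an analysis plan. That would answer a complaint about missing detail. It does not answer the mismatch inside the article, which states an equality hypothesis together with an inferential and power basis that serves only differences.

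Fourth, the no-treatment control and the word 'positive' in H2 already reduce the risk of calling two ineffective programmes equal. That is fair. H1 supplies the comparison with control, and the fix only makes it an explicit condition.

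Finally, a reader might infer from the zero power at 0.2 SD that the sample is useless for H2. The documents propose no such margin, and at their own 'medium' benchmark of 0.5 SD the power is 87-89%.

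**Conclusion.** The point holds as a mismatch between a main hypothesis and the analysis stated for it. Nothing in the Statistical analysis section can support equality between interventions. With 80-85 per arm, a true difference of 0.2 SD gives a non-significant result about 75% of the time, and one of 0.3 SD about half the time.

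The sample is not hopeless. Per pair and unadjusted, it supports a margin of about 0.5 SD with 87-89% power, or about 80% with 68 analysed per arm. A margin of 0.4 SD reaches about 80% only with baseline adjustment at an assumed r of about 0.5 and no attrition. Margins of 0.2 to 0.3 SD are not supported. These figures rest on the assumptions listed with the calculations, above all a true difference of zero and margins that the article does not itself supply.

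The stronger claim, that the trial will report non-significance as equality, is not supported. H1, its comparisons with control and its power calculation are untouched. This should be fixed, but it does not undermine the trial as a whole.

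**What to change.** Choose one of two routes.

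1. **Drop the equality claim.** Delete 'equal' from H2 and from the Discussion. Report the pairwise between-intervention differences as estimates with confidence intervals, and state that non-significance is not evidence of equality.
2. **Make H2 an equivalence question.** Name the main outcome or outcomes to which it applies, since Study design lists seven and no single primary outcome exists. Name the pairs as well, since H2 covers all three while the Discussion compares web and mobile with the group only. Fix and justify a margin before the arms are compared. Claim equivalence for a pair only if the 90% CI of the baseline-adjusted difference lies inside the margin and both arms beat control. State beside the rule which margins the sample can and cannot support, under which assumptions, and that requiring all three pairs lowers power.

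The analysis is described in the future tense, so a margin can be set if the arms have not yet been compared. If they have, only the first route is sound.

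The cost is wording and an analysis rule, with no new participants or data. The downside is that a claim of equality becomes harder to make.

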## Methods/Design

### Study design

This study was a randomized controlled trial (RCT) (Figure 1). Main outcome measures were psychological flexibility, weight, diet quality, eating behavior, perceived stress, depression symptoms, and sleeping habits. Several other variables associated with lifestyle changes, psychological and physiological health was assessed during the study. We were also interested in user experiences of the three novel interventions. The interventions are described below in detail.

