### Measurements

All the participants were measured at the beginning of the study (pre-measurement), after 10 weeks (post-measurement), and after 36 weeks (follow-up). The study included a wide range of psychological, physiological, and technological measurements. The main variables are described below in more detail.

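### Seven unranked main outcomes, three control comparisons and two unranked time points share one 0.05 level, with no hierarchy or adjustment stated

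*Protocol article*

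**What the plan says.** Under Study design the article states: "Main outcome measures were psychological flexibility, weight, diet quality, eating behavior, perceived stress, depression symptoms, and sleeping habits". None is placed above the others. The Statistical analysis section confirms that the plural is meant, because the power calculation covers only one of them: "Analysis was conducted for one of the primary outcome measures, depression symptoms (BDI-II".

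H1, under Aim and main hypotheses, expects improvement over control and adds: "Each intervention group is compared with the control condition separately". With three active arms, that makes three contrasts per outcome.

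The Measurements section gives two post-baseline times: "All the participants were measured at the beginning of the study (pre-measurement), after 10 weeks (post-measurement), and after 36 weeks (follow-up". Neither is called primary, although the sample size refers to the post-measurement.

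On testing, the Statistical analysis section says "The significance level of the study will be set at 0.05", and on method: "Differences in the stability of the outcome measures between the groups will be examined using multiple-group modeling techniques". It does not say whether weeks 10 and 36 are tested separately, and it mentions no multiplicity adjustment and no order of testing.

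**The concern.** A 5% level limits the error of one test. Here it is attached to a trial whose main claim can draw on seven outcomes, three contrasts and two times, and nothing in the text says which result carries the claim. If the text is followed as written, 0.05 is not the error rate of a statement such as: this intervention improved a main outcome. A reader of the results could not tell whether a significant main outcome was the one the trial set out to test or one of many that happened to cross the threshold.

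It also matters for sizing. Only depression symptoms at the post-measurement were used to set the sample size, yet the other six main outcomes have the same standing.

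**Working it through.** **Inputs from the article.** Seven main outcomes (Study design); three active-versus-control contrasts (H1); two post-baseline times (Measurements); level 0.05 (Statistical analysis); 80 to 85 per group.

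**Assumptions, because the article does not give them.** Tests are two-sided. Test statistics for different outcomes correlate between 0 and 0.5, and for the same outcome at the two times 0.6. Contrasts that share a control arm of equal size correlate 0.5, which follows from the design.

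**Step 1: the plan's own figure.** The article expects a 10-point BDI-II difference and says: "A sample size of 320 (80–85 per group) was expected be sufficient at the power level of 1.00". The SD is not given. With 80 per group, two-sided 0.05 and an SD of 8 to 12, power is at least 0.9995, so the stated 1.00 is reproduced. The difficulty is not the power for BDI-II.

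**Step 2: number of tests if each contrast is tested separately.** 7 × 3 = 21 at one time point; 7 × 3 × 2 = 42 at both.

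**Step 3: independence as an upper reference.** The chance of at least one false positive among m tests is 1 − 0.95^m.
- m = 21: 1 − 0.95^21 = 0.659
- m = 42: 1 − 0.95^42 = 0.884

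**Step 4: allowing for correlation.** Correlated normal test statistics were simulated with every true effect set to zero. A result counts as significant if |z| > 1.96. It counts as beneficial if z > 1.96, with all outcomes scored so that positive is better.

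| Setting | Outcome correlation | Any significant result | Significant in the beneficial direction |
|---|---|---|---|
| 1 outcome, 3 contrasts, 1 time | – | 0.125 | 0.06 |
| 7 outcomes, 3 contrasts, 1 time | 0 | 0.61 | 0.36 |
| | 0.3 | 0.56 | 0.30 |
| | 0.5 | 0.49 | 0.25 |
| 7 outcomes, 3 contrasts, 2 times | 0 | 0.81 | 0.54 |
| | 0.3 | 0.77 | 0.45 |
| | 0.5 | 0.70 | 0.39 |

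**Step 5: the mildest reading of the method.** Suppose multiple-group modeling yields one omnibus group-by-time test per outcome, with (4 − 1) × (3 − 1) = 6 degrees of freedom, so seven tests in all. Under independence the error is 1 − 0.95^7 = 0.30. At outcome correlations of 0.3, 0.5 and 0.7 the simulated values are 0.28, 0.24 and 0.19.

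**Step 6: price of a hierarchy.** The detectable standardized difference at 80% power is about (z for 1 − α/2 + 0.842) × √(2/n).
- α = 0.05: (1.960 + 0.842) × √(2/80) = 0.443, and 0.430 with n = 85. The t-based values are 0.446 and 0.432.
- α = 0.05/3: (2.394 + 0.842) × √(2/80) = 0.512, and 0.496 with n = 85. The t-based values are 0.516 and 0.501.

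On the article's own 10-point difference, with 80 per group and an SD of 8 to 12, power would still be at least 0.987 at 0.05/21 and at least 0.979 at 0.05/42.

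**The case against.** Several parts of the defence stand.

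- **Direction.** A reader might infer that, with ineffective interventions, the trial would usually report a false main benefit. The figures do not support that. The larger probabilities count results favouring control as well. In the beneficial direction the chance passes one half only with both times tested and outcomes close to independent, which is implausible for stress, depression, flexibility and sleep.
- **Number of tests.** The article does not fix 42 separate tests. It names multiple-group modeling and leaves the test structure open. At one time point and outcome correlation 0.5, even the two-sided figure is just under one half.
- **Adjustment.** The article does not say that tests will be unadjusted; it is silent. A statistical analysis plan that is not shown may contain an adjustment, and a condensed article may leave that to it. The same holds for choosing one instrument per domain. Psychological flexibility has two questionnaires, eating behavior four, and sleep several sources, so seven is a low count, but the extra instruments are not used in the figures above.
- **Decision rule.** A reader might also infer that H1 is met by any single significant outcome. In H1 the word any refers to the interventions, and the measures are listed together. No rule says that one result suffices, and no rule says otherwise.
- **Arms.** Correcting across three arms is debatable when each intervention answers its own question.

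What the defence does not remove is the choice the article itself makes: seven outcomes of equal standing and two times of equal standing under one level. H1 also calls for a separate control contrast for each arm, so an omnibus test alone could not answer it, and the omnibus reading itself leaves an error of 0.19 to 0.30.

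**Conclusion.** The concern holds in a limited form. The article gives seven main outcomes, three control contrasts and two times equal rank under one 0.05 level and states no adjustment. As written, this does not hold a 5% error rate for the main claim. The size depends on how the tests are built and on correlations that have to be assumed. With no effect of any intervention and separate unadjusted tests, it is about 0.49 to 0.61 at one time and 0.70 to 0.81 at both for any significant result, and about 0.25 to 0.36 and 0.39 to 0.54 for a false benefit. It is about 0.19 to 0.30 with one omnibus test per outcome. Every version is well above 0.05, but the documents do not support saying that a false claim of benefit is more likely than not. Severity: should fix.

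**What to change.** Before any comparison of arms, name one primary outcome and one time point. BDI-II at week 10 is the only combination on which the sample was sized. Test the three active-versus-control contrasts with Holm or Dunnett at 0.05 overall, and report the remaining outcomes and week 36 as secondary.

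If the broad aim is to be kept, an alternative is to retain the seven domains, name one instrument for each and one time point, and apply Holm across the 7 × 3 = 21 contrasts. The first step is then 0.05/21 = 0.0024.

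The article gives December 2013 for the last measurements, so a hierarchy written now comes after data collection. If the data have already been examined by arm, the report should say that the hierarchy was set afterwards and give multiplicity-adjusted p-values for the main results.

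Cost: no new data, only analysis wording. With one primary outcome, the detectable effect per contrast at 80% power rises from about 0.43-0.45 SD to about 0.50-0.52 SD (the higher figures use 0.05/3, the strictest Holm step). The formal primary claim also becomes narrower than the stated aim, which covers metabolic risk factors, psychological flexibility and general well-being.
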